### Statistical analysis

Clinical parametersc laboratory findings and imaging indices of interest will be compared among patients with and without SMuRFs to phenotypically characterize the SMuRF-less group, and identify any particular associations of these biomarkers with the SMuRF-less status. Subsequently, univariate logistic regression analysis will be performed to identify independent predictors of SMuRF-less AMIs. A multivariate logistic regression model will be constructed by forcing univariably significant and clinically relevant variables into the multivariable model. The G*Power software was utilized by a specialist statistician in order to calculate the sample size required to derive statistical significance. It was estimated that to detect an odds ratio > 2 with a prevalence of 15% of SMuRF-less status among AMIs, approximately 75 SMuRF-less patients will be required (with a probability for Type I error: 0.80, and statistical significance level: 0.05). Therefore, 500 patients (with and without SMuRFs) will be included in the present study. An odds ratio > 2 will be interpreted as a prediction of a 2-fold higher probability of having SMuRF-less AMI than an AMI attributed to SMuRFs.

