Baseline patient characteristics of each group will be examined and compared using the chi-square test for categorical variables and the 2-sided Student’s t-test for continuous variables or non-parametric tests (Wilcoxon, Mann-Whitney U etc.), when assumptions of normality are not met. Categorical variables will be represented by frequencies and percentages (%) and continuous variables will be summarized by mean ± standard deviation (SD) or median (1st -3rd quartile), as appropriate. In terms of statistical tests recruited for outcomes calculation, the two groups of patients will be compared to each other to identify clinical, laboratory and imaging biomarkers associated with a higher or lower probability of developing a SMuRF-less AMI. The chi-square test will be used to compare the prevalence of clinical parameters among patients with and without SMuRFs, and the t-test and Mann-Whitney U test will be utilized to compare the mean levels of laboratory and imaging biomarkers between the two groups. As mentioned before, univariate linear and logistic regression analyses will be applied to calculate univariate odds ratios, and then multivariate regression analyses will be performed. Finally, in order to identify the optimal combination of epidemiological, clinical, laboratory and imaging biomarkers associated with SMuRF-less AMIs, supervised machine learning algorithms will be used. The resulting clinical-laboratory prediction models will be evaluated with Receiver Operating Characteristic (ROC) curves.

A time-to-event analysis will be performed to assess whether the absence of SMuRFs is associated with better or worse clinical prognosis of patients (secondary outcome). Event rates will be compared by the long-rank test. Μultivariable Cox proportional hazard models will be utilized to adjust the results for clinically relevant and univariately significant variables. The 2-tailed p value of 0.05 will be considered the significance threshold for all statistical tests. All outcomes will be reported with 95% confidence intervals. Data management and statistical analyses will be conducted using SPSS software, version 26 (IBM SPSS Statistics) and R version 3.4.4 (R Foundation for Statistical Computing, Vienna, Austria).

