## Discussion

‘’Beyond-SMuRF’’ is a prospective cohort trial, enrolling recently hospitalized patients with AMI and aspiring to identify clinical, laboratory and imaging biomarkers associated with SMuRF-less status. So far, suggested polygenic clinical risk-score models seem to underestimate the risk in SMuRF-less patients and are usually incapable of identifying cardiovascular risk factors on top of SMuRFs [18]. Therefore, the rationale of this study is -by comparing clinical, laboratory, echocardiographic and angiographic parameters between the SMuRF-less group and the group of patients with SMuRFs- to assess novel biomarkers as predictors of SMuRF-less AMIs and ultimately generate a risk-stratification tool for this increasingly recognized entity. To our knowledge, this is the first study to comprehensively attempt an in-depth, multiparametric evaluation of the profile of SMuRF-less population with AMI. Although several studies have reported clinical outcomes in SMuRF-less patients, there is a lack of evidence regarding clinical, laboratory and imaging findings in these patients.

Several studies have reported baseline demographic characteristics among patients with and without SMuRFs [3, 11, 18, 19]. Ηowever, no marked differences have been explored so far between the two groups in terms of basic demographic features such as age and sex. Moreover, differences in baseline clinical characteristics and comorbidities have not been thoroughly evaluated on a systematic basis, which adds to the novelty of this study. For instance, rheumatic and autoimmune diseases, as well as abdominal obesity, alcohol consumption and drug use, have been associated with increased cardiovascular risk but have never been assessed as potential absolute explainers of SMuRF-less AMIs [18, 20]. Furthermore, mental health status and psychosocial risk factors have been linked to CAD, but data regarding the association thereof with SMuRF-less status in AMI are lacking [20–24]. Additionally, the lack of physical activity, as well as specific socioeconomic parameters, have been proven drivers of CAD, but never evaluated in the context of SMuRF-less AMIs [24–26].

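### The sample-size statement labels 0.80 as a Type I error, and its unqualified claim to detect an odds ratio of 2 holds only for some kinds of predictor

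*Protocol article*

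**What the plan says.** The sample-size justification is a few sentences in the Statistical analysis section of the protocol article. The target is given as "to detect an odds ratio > 2 with a prevalence of 15% of SMuRF-less status among AMIs". The number and the error rates follow: "approximately 75 SMuRF-less patients will be required (with a probability for Type I error: 0.80, and statistical significance level: 0.05"). The conclusion is "Therefore, 500 patients (with and without SMuRFs) will be included in the present study". The word power does not appear in the statement. No factor, factor prevalence or measurement unit is attached to the odds ratio.

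Later in the same section the threshold is fixed: "The 2-tailed p value of 0.05 will be considered the significance threshold for all statistical tests". Clinical parameters are to be compared by chi-square test and then taken into logistic regression. The Discussion gives examples of clinical factors not yet assessed in this setting, among them "rheumatic and autoimmune diseases, as well as abdominal obesity, alcohol consumption and drug use", without frequencies.

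**The concern.** The significance level is the Type I error rate, so the bracket gives the same quantity two values, 0.80 and 0.05. The only reading that makes sense of 0.80 is power, that is, a Type II error of 0.20.

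Even with the label corrected, the claim is incomplete in a way that affects whether it is true. Power to detect an odds ratio of 2 depends on how common a binary factor is or, for a continuous marker, on the unit of the odds ratio. As written, the sentence can be read as covering any predictor in the study. If a binary factor is uncommon, a reader could take a non-significant result as reasonable evidence against a doubling of the odds when the study had little chance of showing one.

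**Working it through.** **Inputs from the protocol article (Statistical analysis):** odds ratio 2; 15% SMuRF-less; 75 SMuRF-less patients; 500 in total; two-sided 0.05. The 0.80 is read as power.

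**Input not in the article:** p0, the prevalence of the factor in Group B (patients with SMuRFs). I assume 5% to 50%.

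**Step 1: the article's own figures.** 75 / 0.15 = 500, so the total follows exactly from the 75, with 500 − 75 = 425 in Group B. The 75 cannot be reproduced from the stated inputs, because p0 is missing. The two-sided two-proportion formula comes close only for p0 of about 37–41%; at 40% it asks for 77 SMuRF-less patients and 514 in total. Other unstated inputs also come close. A one-sided test at 20% prevalence gives 76. A Wald logistic calculation with 15% as the risk in the unexposed and 25% exposed gives a total of 510. The 75 is therefore under-specified; it is not shown to be wrong.

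**Step 2: power for a binary factor, unadjusted.** An odds ratio of 2 gives p1 = 2·p0 / (1 + p0) in the SMuRF-less group. With p̄ = (75·p1 + 425·p0) / 500,

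- s0 = √[p̄(1 − p̄)(1/75 + 1/425)]
- s1 = √[p1(1 − p1)/75 + p0(1 − p0)/425]
- power = Φ[(p1 − p0 − 1.96·s0) / s1]

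At p0 = 0.10: p1 = 0.1818, p̄ = 0.1123, s0 = 0.0395, s1 = 0.0469. Power = Φ[(0.0818 − 0.0774) / 0.0469] = Φ(0.09) ≈ 0.54.

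At p0 = 0.40: p1 = 0.5714, p̄ = 0.4257, s0 = s1 = 0.0619. Power = Φ[(0.1714 − 0.1213) / 0.0619] = Φ(0.81) ≈ 0.79.

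The second column below uses the Wald test of the log odds ratio, Φ[ln 2 / SE − 1.96] with SE² = 1/[75·p1(1 − p1)] + 1/[425·p0(1 − p0)]. The last column solves each formula for the odds ratio that gives 80% power.

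| Prevalence in Group B (assumed) | Power, two proportions | Power, Wald | Odds ratio detectable with 80% power |
|---|---|---|---|
| 50% | 77% | 75% | 2.05–2.10 |
| 40% | 79% | 78% | 2.02–2.04 |
| 30% | 78% | 78% | 2.04 |
| 20% | 71% | 72% | 2.14–2.17 |
| 15% | 64% | 65% | 2.25–2.30 |
| 10% | 54% | 53% | 2.48–2.56 |
| 5% | 37% | 34% | 3.07–3.24 |

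Simulated chi-square tests (200,000 runs per point) gave 79% at 40%, 78% at 30%, 71% at 20%, 53% at 10% and 35% at 5%.

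**Step 3: other readings of the 15%.** If prevalence is taken over all 500 patients, with 15% as the overall SMuRF-less share, the Wald calculation gives 77% at 30%, 70% at 20%, 50% at 10% and 30% at 5%. The detectable odds ratios rise to about 2.6–2.7 at 10% and 3.4–3.6 at 5%. If 15% is the risk in the unexposed, power is 83% at 30% and 86% at 40–50%, but still 74% at 20%, 51% at 10% and 31% at 5%.

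**Step 4: continuous marker, odds ratio 2 per standard deviation.** Power = Φ[ln 2 · √(500 × 0.15 × 0.85) − 1.96] = Φ[0.693 × 7.98 − 1.96] = Φ(3.57) > 0.99. The total needed for 80% power is (1.96 + 0.84)² / (0.15 × 0.85 × 0.693²), about 129. With an assumed R-squared of 0.5 on the other covariates, power at 500 is still 97%.

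**Step 5: adjustment, binary factor.** With an assumed R-squared of 0.2, the Wald power of Step 3 (15% as the overall share) falls to about 66% at 50% prevalence and 41% at 10%.

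**The case against.** The mislabel is a slip that no analyst would act on: 0.05 stands in the same bracket and a two-tailed 0.05 is repeated later. No threshold, analysis or patient number changes. That is right about the consequences for analysis, but the statement is still wrong in the study's only sample-size justification.

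The article does not say that 80% power holds for every factor. It reports one generic calculation, done in G*Power by a statistician, and a condensed article may leave the missing input to the full document. For common factors the detectable odds ratio is 2.0–2.1, which fits the claim. This largely stands: it rules out calling the 75 or the 500 an error. It does not rescue the unqualified wording, since the claim holds for some of the study's predictors and not for others.

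A reader might infer that 500 patients are too few, or that a large part of the primary outcome is underpowered. The documents do not support either. Many of the laboratory, echocardiographic and angiographic parameters are continuous, and power for them is above 99% on a per-SD scale. The article gives no frequencies for the factors it names, and its list also includes abdominal obesity and alcohol consumption. Nor is it a fault that 75 is only an expected count; the article says approximately. The commitment to 95% confidence intervals for all outcomes will also show imprecision where it exists.

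**Conclusion.** The point holds in two limited parts. First, 0.80 is mislabelled as a Type I error; this needs no assumption. Second, the claim about an odds ratio above 2 is stated without the predictor on which it depends. For a binary factor present in 30–40% of Group B the claim is essentially met. The shortfall is moderate at 20% and substantial at 10% and 5%, where power is about one half and one third. At prevalences of 15% or less, no variant tried reaches 80%, including one-sided tests and the reading of 15% as the risk in the unexposed. Those prevalences are my assumptions, as is the R-squared used for adjustment. For continuous markers per standard deviation there is no shortfall.

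**What to change.** In the Statistical analysis section:

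- Replace the error-rate bracket with power 0.80 and two-sided Type I error 0.05.
- State the factor prevalence, or the predictor unit, behind the odds ratio of 2, and limit the claim to that case.
- Add a sentence that for less common binary factors the odds ratio detectable with 80% power at 500 patients is larger: about 2.2 at 20% prevalence, 2.5–2.7 at 10% and 3.1–3.6 at 5%, and larger still after adjustment.

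The total stays at 500. The cost is one paragraph of text and a less favourable stated power for uncommon factors.

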## Background

Acute myocardial infarction (AMI) remains the leading cause of mortality worldwide [1]. The incidence of coronary artery disease (CAD) and -its most adverse manifestation- AMI, has been proven to rise along with the increasing prevalence of major cardiovascular risk factors, such as obesity, smoking, and hypercholesterolemia [2]. These comorbidities have been well recognized as risk factors of coronary artery disease (CAD) and are often used to evaluate the risk of sustaining an acute coronary event, including AMI. Furthermore, the primary and secondary prevention of AMIs has primarily focused on the modification and treatment of standard modifiable risk factors (SMuRFs), namely smoking, diabetes mellitus, dyslipidaemia, and hypertension [2]. However, recent registries indicate a growing population of patients suffering an acute coronary syndrome (ACS) without any SMuRF (SMuRF-less patients) [3–6]. Over the past decade, the prevalence of such cases among patients presenting with ST-segment elevation myocardial infarction (STEMI) has increased from 13 to 27% in a large, national registry [3].

To date, scientific evidence on the pathogenesis and etiology of SMuRF-less AMI remains limited, although it constitutes an increasingly recognized clinical entity. A popular hypothesis implicates systematic inflammation and high levels of intra-coronary pro-inflammatory cytokines, but data are scarce. Pro-inflammatory and atherosclerosis biomarkers, such as lipoprotein (a) [Lp(a)], C-reactive protein and fibrinogen, have been shown to have higher specificity in predicting worse prognosis of AMI in SMuRF-less patients, as compared to patients with SMuRFs, but no studies have been conducted to investigate their role as predictors of SMuRF-less AMIs [4, 7]. Furthermore, large observational studies have indicated several demographic features potentially linked to SMuRF-less status in AMI, but the results are contradictory, probably due to marked heterogeneity in studied populations [8–10]. Hence, pinpointing sensitive clinical and laboratory parameters, as well as diagnostic approaches, for the prediction of AMI in patients without SMuRFs is crucial, as it concerns an increasing proportion of patients with CAD, who are rather under-represented in registries and clinical trials of cardiovascular risk-assessment [11].

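### The plan misreads odds ratios above 2 as a two-fold higher probability of SMuRF-less AMI than of AMI attributed to SMuRFs

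*Protocol article*

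**What the plan says.** In the protocol article, Methods, Statistical analysis, the study is sized "to detect an odds ratio > 2 with a prevalence of 15% of SMuRF-less status among AMIs". The text states that "approximately 75 SMuRF-less patients will be required" and reaches a total of 500. The paragraph ends with a rule for reading the result: an odds ratio above 2 "will be interpreted as a prediction of a 2-fold higher probability of having SMuRF-less AMI than an AMI attributed to SMuRFs".

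The odds ratios come from univariable and then multivariable logistic regression of SMuRF-less status among patients who all have an AMI. Study design and population defines the comparison group by a history, treatment or diagnosis of at least one of four risk factors. Nothing elsewhere in the article corrects the rule or converts odds ratios to probabilities.

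**The concern.** The rule contains two separate errors.

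- **Scale.** An odds ratio is treated as a ratio of probabilities. The two are close only when the outcome is rare, and 15% is not rare enough.
- **Contrast.** The odds ratio compares patients with the factor to patients without it. The sentence instead compares the two outcome categories, SMuRF-less AMI and AMI with SMuRFs, and has no unexposed group in it.

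The word *attributed* also suggests a cause, although group membership rests only on the presence of a risk factor.

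This is the only rule the article gives for reading its main association measure, and an odds ratio of 2 is the effect the study is sized to find. A report that followed it would tell readers that a factor makes SMuRF-less AMI twice as probable as AMI with SMuRFs, when most patients with that factor would still have SMuRFs. The rule is stated text, so it is not a detail left to an analysis plan.

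**Working it through.** **Inputs.** From Statistical analysis: odds ratio (OR) 2, SMuRF-less prevalence 15%, 75 SMuRF-less patients, 500 in total. From Background: a STEMI registry figure that "has increased from 13 to 27% in a large, national registry". The article gives no prevalence for any factor; 50% is assumed where one is needed. All calculations take a single binary factor without covariates.

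**The plan's own figure.** 75 / 0.15 = 500, which leaves 500 − 75 = 425 patients with SMuRFs. The total reproduces, and the interpretation rule is not an input to it.

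**Formulas.** Let p0 and p1 be the probabilities of being SMuRF-less without and with the factor.

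- p1 = OR × p0 / (1 − p0 + OR × p0)
- risk ratio = p1 / p0
- SMuRF-less to SMuRF ratio among the exposed = p1 / (1 − p1)

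The sentence can be read in two ways. They give different errors and should not be combined.

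**Reading A: OR 2 taken as a risk ratio of 2 (exposed against unexposed).**

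- 15% in the unexposed: p1 = 0.30 / (0.85 + 0.30) = 0.261; risk ratio 0.261 / 0.15 = 1.74.
- 15% overall, factor in half the patients (assumed): solving (p0 + p1) / 2 = 0.15 gives p0 = 0.107 and p1 = 0.193; risk ratio 1.81.
- Registry range used as p0: at 13%, p1 = 0.26 / 1.13 = 0.230, risk ratio 1.77; at 27%, p1 = 0.54 / 1.27 = 0.425, risk ratio 1.57.
- OR at which the risk ratio reaches 2, with 15% in the unexposed: p1 must be 0.30, so OR = (0.30 / 0.70) / (0.15 / 0.85) = 2.43.

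**Reading B: the literal words (SMuRF-less against SMuRF AMI among the exposed).** Two-fold means p1 / (1 − p1) = 2, so p1 = 2/3 = 66.7%.

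| Setting | p1 at OR 2 | Actual ratio, SMuRF-less to SMuRF | 66.7% divided by p1 |
|---|---|---|---|
| 15% in the unexposed | 26.1% | 0.261 / 0.739 = 0.35 | 2.6 |
| 15% overall, factor in 50% (assumed) | 19.3% | 0.193 / 0.807 = 0.24 | 3.5 |

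- With the registry range of 13% to 27% as p0, the actual ratio is 0.30 to 0.74, still below 1.
- With 15% in the unexposed, the two outcomes become equally probable at OR = 1 / (0.15 / 0.85) = 5.67. SMuRF-less AMI becomes twice as probable only at OR = 2 / (0.15 / 0.85) = 11.3.
- At OR 2 the literal reading is right only when the unexposed odds are 1, that is, when half of the unexposed are SMuRF-less.

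**The case against.** The strongest reply is that this is loose wording with modest consequences. Elsewhere the same section speaks of biomarkers linked to a higher or lower probability of SMuRF-less AMI. That is a contrast across biomarker levels, so Reading A is probably what was meant, and there the gap is only 1.74 to 1.81 against 2. With 15% printed in the same paragraph, readers could see that SMuRF-less AMI is not the commoner outcome. The Limitations section already rules out causal conclusions. The sentence changes no estimator, test or threshold and can be put right at reporting.

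Much of this stands. The intent may well be Reading A, and it is not established that the final report would state Reading B. The causal wording is a minor matter. But Reading B is what the words say, Reading A is also wrong at 15%, and nothing in the article replaces the rule.

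A reader might go further and infer that the rule overstates every result of the study. The documents do not support that:

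- The rule covers only odds ratios above 2.
- The odds ratios, their intervals and p values remain valid as odds ratios.
- The group comparisons, ROC curves, log-rank test and Cox models do not use it.
- Under Reading A, at least two-fold is no overstatement once the odds ratio reaches 2.43 with 15% in the unexposed. For a rare outcome the error nearly vanishes: at 1%, OR 2 gives a risk ratio of 1.98.

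**Conclusion.** The point holds as a misstatement of what odds ratios above 2 mean. As a risk ratio, OR 2 corresponds to about 1.74 with 15% in the unexposed, or about 1.81 with 15% overall and a factor assumed present in half the patients. Taken literally, the rule implies 66.7% SMuRF-less among the exposed where the figure would be about 19% to 26%, and it gets wrong which outcome is the more probable.

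The sizes rest on the plan's 15%, on a single binary factor and, for the second setting, on the assumed 50% factor prevalence. The finding itself does not depend on these choices: an odds ratio is not defined by that contrast at any prevalence. The damage is confined to the conclusion drawn from an odds ratio; the data, the estimates and the sample size are untouched.

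**What to change.** Replace the last sentence of the sample size paragraph in Statistical analysis with:

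> Among patients with AMI, an odds ratio of 2 means that the odds of being SMuRF-less are twice as high in patients with the factor (or per stated unit) as in those without it.

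Drop the word *attributed* and refer simply to AMI in patients with SMuRFs. If the investigators want to speak of probabilities, they can add predicted probabilities or risk ratios derived from the same logistic model. This is optional, because correctly described odds ratios are sufficient.

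The cost is one sentence. The optional addition is a routine step after model fitting, in software already planned (R), and needs no new data or change of design.

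### Student's t-test is named with no provision for unequal variances, although the groups are expected to be about 75 and 425; Welch's test should be named instead (minor)

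*Protocol article*

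**What the plan says.** All quotes are from the Statistical analysis section of the protocol article.

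- For baseline characteristics the plan uses the "2-sided Student’s t-test for continuous variables", with rank tests as the alternative. Non-normality is the only stated reason to leave Student's test.
- For the outcome comparisons, "the t-test and Mann-Whitney U test will be utilized to compare the mean levels of laboratory and imaging biomarkers between the two groups". The variant of the t-test is not named.
- Group sizes follow from the sample-size paragraph: "with a prevalence of 15% of SMuRF-less status among AMIs, approximately 75 SMuRF-less patients will be required", in a total of 500.
- "The 2-tailed p value of 0.05 will be considered the significance threshold for all statistical tests", and "All outcomes will be reported with 95% confidence intervals".

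The section on data collection and study procedures makes the comparison of clinical, laboratory and imaging parameters between the two groups the primary outcome. Nothing in the article mentions equal or unequal variances.

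**The concern.** Student's name ordinarily denotes the equal-variance two-sample t-test. That test pools the two variances with weights close to the group sizes, so at 75 against 425 the pooled variance is almost entirely that of the larger group. The true standard error of the difference, however, is dominated by the smaller group. If the smaller group is less variable, the standard error is too large: the test is conservative and the interval too wide. If it is more variable, the standard error is too small: the test rejects too often and the interval is too narrow. With groups of similar size this hardly matters; at roughly 1 to 5.7 it can.

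At stake are the p-values and 95% confidence intervals of the mean comparisons that make up part of the primary outcome.

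Unequal spread is plausible for some variables. Under Study design and population, Group A excludes patients with known hypertension, diabetes, hypercholesterolaemia or smoking, and also those whose diabetes is found by HbA1c during the admission. That cuts off the upper range of HbA1c in Group A, and related variables may narrow as well.

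**Working it through.** **Inputs from the article.** Total 500; SMuRF-less share 15%; two-sided alpha 0.05.

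**Input not in the article.** The SD ratio r = SD(A)/SD(B). It is assumed, and shown from 0.67 to 1.5. Data are taken as normal, and Group B's SD is set to 1.

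**Group sizes.** 500 × 0.15 = 75 and 500 − 75 = 425, a ratio of 425/75 = 5.67. This reproduces the plan's figure of about 75.

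**Formulas.**

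- True SE = √(r²/75 + 1/425)
- Pooled SE (expected) = √{[(74r² + 424)/498] × (1/75 + 1/425)}
- k = pooled SE / true SE
- Type I error ≈ 2 × [1 − Φ(1.96k)]

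**Worked case, r = 1.5.** True SE = √(0.0300 + 0.00235) = 0.180. Pooled SE = √(1.1857 × 0.015686) = 0.136. So k = 0.758, 1.96k = 1.486, and the Type I error is 13.7%.

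**Worked case, r = 0.67.** True SE = √(0.005985 + 0.002353) = 0.0913. Pooled SE = √(0.9181 × 0.015686) = 0.1200. So k = 1.314, 1.96k = 2.576, and the Type I error is 1.0%.

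**Range, with a simulation of 200,000 runs per ratio.**

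| r (A/B) | k | Student, formula | Student, simulated | Student 95% CI coverage | Welch, simulated |
|---|---|---|---|---|---|
| 0.67 | 1.314 | 1.0% | 1.0% | 99.0% | 5.0% |
| 0.8 | 1.168 | 2.2% | 2.2% | 97.8% | 5.0% |
| 0.9 | 1.077 | 3.5% | 3.5% | 96.5% | 5.0% |
| 1.0 | 1.000 | 5.0% | 4.9% | 95.1% | 4.9% |
| 1.1 | 0.935 | 6.7% | 6.7% | 93.3% | 5.1% |
| 1.25 | 0.856 | 9.3% | 9.3% | 90.7% | 5.0% |
| 1.5 | 0.758 | 13.7% | 13.8% | 86.2% | 5.0% |

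**Power at r = 0.67, difference 0.25 (in Group B SDs).**

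- Student: the difference must exceed 1.96 × 0.1200 = 0.2352. Power ≈ Φ[(0.25 − 0.2352)/0.0913] = Φ(0.16) ≈ 56%.
- Welch: power ≈ Φ(0.25/0.0913 − 1.96) = Φ(0.78) ≈ 78%.

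**Cost of Welch if the SDs are equal.** At a 0.35 SD difference, simulated power is 79.7% with Student and 79.1% with Welch, a loss of 0.6 points.

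**Two further checks by simulation at 75 against 425 (5,000 runs per ratio).**

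- Mann-Whitney rejects 1.8% at r = 0.67, 7.0% at 1.25 and 9.3% at 1.5, so the rank test is also affected by unequal spread.
- The Wald test from a univariate logistic regression on the same kind of data rejects 0.9%, 9.4% and 13.0% at those ratios, almost the same as Student's test.

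**The case against.** The strongest reply is that an article condenses the plan. Student's t-test is often a loose label for any two-sample t-test, the article never mentions pooling, and the biomarker sentence leaves the variant open. The choice of form, or a preliminary variance test, may be in a document not shown. A t-test that moves to Welch when Levene's test is significant held 4.8% to 5.7% in simulation over ratios 0.67 to 2.0. This stands in part: the equal-variance form is a reading of the name, most directly for the baseline comparisons. But the article does name a test and does state when to leave it, and unequal variance is not among the reasons.

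A second reply is that no SD is given for either group, so large errors are hypothetical. That stands. A 10% difference in SD moves 5% only to 3.5% or 6.7%. The group definitions support a narrower Group A for some variables; they give no reason to expect a wider one. A reader might infer from the 9.3% and 13.7% figures that false positives are the likely result. The documents do not support that.

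A reader might also infer that these t-tests decide which variables enter the multivariable model. The article does not say so. It places the univariable significance rule directly after univariate logistic regression, and naming Welch would leave that selection step unchanged.

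Finally, the t-test covers only continuous variables judged normal, which limits the reach of the point.

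**Conclusion.** The point holds as a minor weakness. A named test with no provision for unequal variances is a poor choice at an expected 75 against 425, when an alternative that keeps its nominal size is available at almost no cost. The error is material only if the SD ratio is about 0.8 or less, or about 1.25 or more. The more plausible direction here, for some variables, is a narrower Group A. The consequence is then lost power and over-wide intervals in the comparisons meant to characterise the small group.

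This rests on three assumptions: that Student's test means the equal-variance form, that the biomarker sentence refers to the same test, and that spread differs by the amounts tabulated. The article confirms none of them, and it should not be read as showing that the primary comparisons will be wrong.

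**What to change.** In the Statistical analysis section, replace "2-sided Student’s t-test for continuous variables" with Welch's unequal-variance t-test. Name the same test in the biomarker sentence, and report the Welch 95% confidence interval for each difference in means. Keep the rank test for clearly skewed variables, but state that it too is affected by unequal spread, so that it is not taken as the remedy.

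The change is one of wording. It needs no extra patients or data, and costs under 1 point of power if the SDs are equal. It does not alter the logistic regression stage. Because the univariate logistic p-values behave much like Student's, a Welch p-value and an odds-ratio p-value for the same variable may differ where spread is unequal. A sentence saying which one is the primary result would avoid confusion.
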